## Summary of known and potential risks and benefits

Already documented risk of remifentanil PCA are maternal respiratory depression, nausea/vomiting and itching. Known risks of epidural analgesia are hypotension, increased use of oxytocin and increased risk of instrumental delivery.

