### Secondary study parameters/endpoints

If RPCA is equivalent to EA with respect to pain appreciation the next endpoint will be the costs of both interventions. For both strategies the cost of perinatal care for mother and child, starting at the onset of labor and ending ten days after delivery, will be registered and compared (without discounting). The costs consist of costs of delivery/childbirth (course and mode of delivery), postnatal maternal care (hospitalization, outpatient visits), neonatal care (admission to NICU/neonatology ward, outpatient visits) and primary care (midwife, general practitioner, maternity care).

Maternal outcome

- Morbidity (post spinal headache, postpartum haemorrhage (>1 litre or administration of blood products), uterine rupture, eclampsia, amniotic fluid embolism, myocardial infarction, admission to ICU, other (defined as major maternal morbidity by local researchers).
- Maternal mortality
- Prolonged maternal admission. Admission in days measured from delivery of the child.
- Diagnosis during admission: endometritis, suspected infection, UTI treated with antibiotics, wound infection treated with antibiotics, obstructed bowel disease, pneumonia, trombo-embolic complications, hypertensive disorders, postpartum haemorrhage, post caesarean, pre-eclampisa/HELLP, admission due to condition child, other.

Maternal parameters

- pain scores, measured hourly from start of labor using a VAS scale
- pain appreciation scores, measured hourly from the start of labor and after start of pain relief every 15 min in the first hour and hourly after that on a VAS scale.
- satisfaction with pain, measured on a scale of 0-10 after delivery
- side effects, during administration of pain relief
  - hypotension (systolic blood pressure <90 mmHg of <25% below baseline)
  - nausea/vomiting (none, mild, moderate, severe)
  - itching (none, mild, moderate, severe)
  - respiratory depression (respiratory rate <8/min)maternal fever during labor (temperature >38°C)

Neonatal outcome

- Apgar scores ≤ 6 after 1 and 5 minutes
- Umbilical cord pH < 7.10
- Admissions to the neonatal ward

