# STATISTICAL ANALYSIS

## Descriptive statistics

- 1. Maternal age: continuous, quantitative
  2. ASA physical status: continuous, quantative (1-5)
  3. Body Mass Index: continuous, quantative
  4. Parity: categorical, quantitative: (nulliparous / multiparous)
  5. Previous cesarean delivery: categorical, quantitative (yes/no)
  6. Gestational age: continuous, quantitative
  7. Maternal origin: categorical, quantitative (Caucasian, Mediterranean, Creole, Asian)
  8. Educational level: categorical, quantitative
  9. Number of fetuses: categorical, quantitative (1-3)
  10. Fetal condition at time of request pain relief: categorical, quantitative (optimal, non reassuring, fetal tachycardia)
  11. Start of labor: categorical, quantitative (spontaneous/induction)
  12. Use of oxytocin: categorical, quantitative (yes/no)

Mode of delivery: categorical, quantitative (vaginal delivery, instrumental delivery,

cesarean section)

- 1. Indication for cesarean section/ instrumental delivery: categorical, quantitative Duration first stage of labor: continuous, quantitative
  2. Duration second stage of labor: continuous, quantitative
  3. Time from request to start of analgesia: continuous, quantitative
  4. Duration of analgesia: continuous, quantitative
  5. Conversion from epidural analgesia to RPCA: categorical, quantitative (yes/no)
  6. Conversion from RPCA to epidural analgesia: categorical, quantitative (yes/no)
  7. Type of medication used for epidural analgesia: categorical, quantitative
  8. Increases or decreases in bolus dose for RPCA: categorical, quantitative
  9. Maternal pain scores: continuous, quantitative (0-10)
  10. Maternal pain appreciation scores: continuous, quantitative (0-10)
  11. Maternal satisfaction with analgesia: continuous, quantitative (0-10)
  12. Maternal temperature: continuous, quantitative
  13. Start of intravenous broad spectrum antibiotics; quantitative (yes/no)
  14. Maternal saturation: continuous, quantitative
  15. Maternal respiratory depression: categorical, quantitative (yes/no)
  16. Oxygen administered: categorical, quantitative (yes/no)
  17. Maternal hypotension: categorical, quantitative (yes/no)
  18. Nausea/vomiting: categorical, quantitative (mild, moderate, severe)
  19. Itching: categorical, quantitative (mild, moderate, severe)
  20. Postpartum hemorrhage >1000 ml: categorical, quantitative (yes/no)
  21. Major maternal complication
  22. Post spinal headache: categorical, quantitative (yes/no)

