centre and parity. First, the epidural and remifentanil group will be compared. Relative risks and 95% confidence intervals will be calculated for the relevant outcome measures. Categorical variables will be tested with the Chi-square test or Fisher’s exact test. Continuous variables will be tested with the Mann-Whitney U test. Time to delivery will be assessed using Kaplan-Meier analysis. Pain scores will be analyzed separately. We will report on pain during labor (area under the curve and mean pain score), worst pain during labor, pain scores at request pain relief. The analysis will be repeated on a par protocol basis. Subsequently, planned subgroup analysis will be done for nulliparous versus parous women, previous caesarean section, preterm labor (32 to 34 weeks and 34-37 weeks) and term labor (37-42 weeks), spontaneous versus induced labor, maternal educational level, maternal age (under 35 years versus over 35 years), multiple pregnancy. We will then use decision analysis to evaluate which intervention strategy, ie epidural analgesia or remifentanil is preferred in women who need analgesia during labor.

The low risk women will be included and analyzed in a separate trial. In the Dutch system with midwifery care and home births, there might be a difference in expectation of women with regard to pain during labor.

To be able to convince both primary and secondary care providers, these groups will be analyzed separately.

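### Nausea/vomiting and itching are graded none to severe, but section 8.1 gives them an unordered test and its variable list omits the grade 'none'

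*Protocol*

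**What the plan says.** Protocol section 6.1.2 (secondary endpoints) lists side effects during administration of pain relief. Two of them have four ordered grades: "nausea/vomiting (none, mild, moderate, severe)" and "itching (none, mild, moderate, severe)".

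The variable list in section 8.1 gives the same two outcomes as "Nausea/vomiting: categorical, quantitative (mild, moderate, severe)" and "Itching: categorical, quantitative (mild, moderate, severe)". Both are typed as categorical, and the grade 'none' is absent from both lines.

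The analysis text in section 8.1 then fixes the tests by variable type:
- "Categorical variables will be tested with the Chi-square test or Fisher’s exact test".
- "Continuous variables will be tested with the Mann-Whitney U test".
- "Relative risks and 95% confidence intervals will be calculated for the relevant outcome measures".

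No trend or ordinal method is named, and no cut point is given for turning a graded outcome into a relative risk. The same section says that the analysis is by intention to treat, stratified for centre and parity.

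Section 5.3 states: "Already documented risk of remifentanil PCA are maternal respiratory depression, nausea/vomiting and itching". Maternal side effects are a secondary objective (section 2).

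**The concern.** A chi-square or Fisher test on two groups and four grades treats the grades as interchangeable labels. It spreads the evidence over three degrees of freedom and does not say in which direction the groups differ. If one method makes the symptom both more frequent and more severe, a test that uses the order will usually detect it more readily with the same data. The protocol plans to collect the grading, and the test it names then discards the order.

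The two sections also disagree on the scale, with four grades in 6.1.2 and three in 8.1.

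What is at stake is the ability to show a difference on two side effects that the protocol itself associates with RPCA. They are secondary outcomes and play no part in the sample size.

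**Working it through.** **1. Number of women, from section 4.4.** The protocol's figures are for pain appreciation: difference 1 point (10% of a 10-point scale), SD 2.2, two-sided alpha 0.05, power 90%.

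- n per group = 2 × 2.2² × (1.960 + 1.282)² / 1² = 101.7, so 102, as stated.
- Dilution for 10% and 30% cross-over or non-compliance: 102 / (1 − 0.10 − 0.30)² = 102 / 0.36 = 283.3, so 284 per group and 568 in total, as stated.
- 568 / 0.5 = 1136 randomised, as stated.

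The side effects are recorded while pain relief is given, so 284 treated women per group is the relevant size. The protocol gives no rate, effect or power for nausea/vomiting or itching. Everything below rests on assumed grade distributions.

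**2. Upper limit of the loss.** Compare a 1-df and a 3-df chi-square test at equal noncentrality, two-sided 5%. A noncentrality of 7.85 gives 80% power on 1 df and 64.5% on 3 df. Over all noncentralities the largest gap is 17.0 points (66.2% against 49.2%). At 99% power on 1 df the gap is 2.7 points.

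**3. Simulated power under a consistent shift.** The second group has all cumulative odds multiplied by one odds ratio (OR). For grades 70/15/10/5% and OR 1.5, the odds of any symptom go from 0.30/0.70 = 0.429 to 0.643, so the rate goes from 30% to 39.1%. The shifted grades are 60.9/18.2/13.6/7.3%. Power in percent, 284 per group:

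| Grades none/mild/moderate/severe, OR | Chi-square, 3 df | Wilcoxon | Gap | Any v none |
|---|---|---|---|---|
| 85/9/4/2, 1.75 | 57.5 | 74.9 | 17.4 | 74.4 |
| 70/15/10/5, 1.25 | 16.4 | 24.9 | 8.5 | 24.3 |
| 70/15/10/5, 1.5 | 47.8 | 65.1 | 17.3 | 62.8 |
| 70/15/10/5, 2.0 | 94.7 | 98.5 | 3.8 | 98.1 |
| 50/25/15/10, 1.5 | 57.9 | 74.6 | 16.7 | 66.6 |
| 50/25/15/10, 2.5 | 100.0 | 100.0 | 0.0 | 100.0 |

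Each row is 20,000 simulated trials, a standard error of at most √(0.25/20,000) = 0.35 points per figure. Values slightly above 17.0 therefore agree with the limit in step 2.

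**4. What a relative risk for any symptom recovers.** For 30% against 39.1%, the difference is 0.0913, the pooled rate 0.3457 and the standard error √(2 × 0.3457 × 0.6543 / 284) = 0.0399. Then z = 2.29 and power ≈ Φ(2.29 − 1.96) = 63%, in line with the table. The share of the gap recovered is:
- 15% with any symptom, OR 1.75: 16.9 of 17.4 points, 97%.
- 30%, OR 1.5: 15.0 of 17.3 points, 87%.
- 50%, OR 1.5: 8.7 of 16.7 points, 52%.

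**5. When the grades do not shift together** (284 per group, control 70/15/10/5%):
- Severe rises from 5% to 12%, 'none' stays at 70%, mild and moderate fall to 10% and 8%: chi-square 84.1%, Wilcoxon 8.9%.
- Mild rises from 15% to 25% and 'none' falls to 60%: chi-square 73.2%, Wilcoxon 55.0%.

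In the first pattern a comparison of the severe grade alone has difference 0.07, pooled rate 0.085 and standard error √(2 × 0.085 × 0.915 / 284) = 0.0234. Then z = 2.99 and power ≈ Φ(1.03) = 85%. In the second pattern, any symptom against none has 70.4%.

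**The case against.** The strongest reply is that the same part of section 8.1 promises relative risks with confidence intervals. A relative risk needs a binary outcome, and it shows direction and size. If the grades are cut at any against none, most of the loss disappears when symptoms are uncommon, as step 4 shows. This stands in part. The protocol does not say that these outcomes are cut, or where, and the recovery is only about half when half the women have symptoms.

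Second, chi-square and Fisher are valid tests, and neither test is better against every pattern. Step 5 shows that an ordered test alone could miss a rise confined to severe cases. This stands, and the fix has to cover it.

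A reader might infer three stronger things that the documents do not support:
- **A fixed loss of power built into the plan.** No rates or effects are given, and the loss can be nil or change sign.
- **Women without symptoms would be left out of the comparison.** The lines lacking 'none' belong to a shorthand list of variable types. The endpoint definition in 6.1.2 includes the grade, and the analysis is by intention to treat. This is a mismatch to reconcile and does not show that women would be excluded.
- **A non-significant result would be reported as no difference in side effects.** The equivalence claim concerns pain appreciation only. Section 5.2 also lists itching among epidural complications, so an excess under RPCA is not given for that symptom.

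**Conclusion.** The point holds as a minor one. The protocol names a test for these two outcomes that ignores their order, and sections 6.1.2 and 8.1 disagree on whether 'none' is a grade. A separate analysis plan could add detail, but the test named here does not suit the scale, and the mismatch is visible in the protocol itself.

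The size is 0 to about 17 points of power against an ordered test. This assumes 284 treated women per group, four grades, a proportional-odds shift, and control rates of any symptom between 15% and 50%. The loss is largest when the ordered test has about 65% power, and it vanishes when power is very high. For the separately analysed low-risk women (102 treated per group, section 4.4.1) the pattern is similar: 51.5% against 69.3% for grades 70/15/10/5% and OR 2.0. The advantage does not carry over to effects confined to one grade.

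**What to change.** In section 8.1:

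1. Restore 'none' in the lines for nausea/vomiting and itching, so that they match section 6.1.2.
2. State that both outcomes are analysed on all four grades with an ordered method. This can be a Wilcoxon-Mann-Whitney test stratified for centre and parity, or a proportional-odds model giving a common odds ratio with 95% confidence interval.
3. State the cut points for the relative risks: any symptom against none, and severe against all lower grades, each with a 95% confidence interval.
4. Tabulate the four grades by group.

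The cost is a few lines of text, with the same data and no extra women. The one drawback is that the ordered test is weaker than chi-square when a single grade changes. The severe-grade relative risk (about 85% power in the example in step 5) and the tabulated grades cover the case that matters most for safety.

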Equi-analgesia or equi-efficacy among the treatment groups is an essential part of the study as it is the primary end-point of analgesic treatment during labor. The definition of equi-analgesia in our study is a difference in pain appreciation (VAS score) among the two study groups of 10% or less. Preliminary data in perioperative patients on PCA opioid treatment ([name], oral communication) indicate that at VAS scores ranging from 4 to 8 (the expected range in our study), changes (i.e. increases) in pain score of 10% or larger will prompt an action of the patient (i.e. she will require additional pain relief by pressing the PCA button). Extrapolating these data to the current study suggests that at VAS score differences of 10% or greater clinical differences in pain appreciation may be assumed.

It is expected that economical evaluation of both strategies will show a significant reduction in costs of this innovative strategy.

Other outcome measures are pain scores, patient satisfaction, maternal and neonatal outcome and validated questionnaires.

This study considering cost effectiveness of RPCA as first choice analgesia versus EA could strongly improve the care for 180.000 women, giving birth in the Netherlands yearly (according to LVR data (2008) 30% of pregnant women under care in a hospital need pain relief during labor), by giving them access to pain relief during labor if needed, 24 hours a day.

In the guidelines of gynecologist and midwives it is recommended to discuss the opportunities of pain relief during labor antenatal (1).

An estimation of costs for RPCA versus EA shows a decrease of 64 euro per patient. The difference in costs is due to the extra costs of anesthetic staff and nurses, required when EA is given. Nationwide this could potentially save 1.2-4.6 million euro per year, depending on the percentage of women needing pain relief, varying respectively from 10-40%.

The results of the study will provide insight on whether RPCA in women in labor will reduce costs as compared to EA, assuming RPCA is equivalent to EA with respect to pain appreciation scores. At present, no clinical study has been published or undertaken to investigate this issue.

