**Economic analysis:**

The costs consist of costs of delivery/childbirth (course and mode of delivery), postnatal maternal care (hospitalization, outpatient visits), neonatal care (admission to NICU/neonatology ward, outpatient visits) and primary care (midwife, general practitioner, maternity care).

Costs of delivery/childbirth are estimated by a detailed cost price analysis in which units of resource use (time of hospital staff, materials, equipment) are valued using cost per unit estimates comprising "true economic" costs, i.e. including shares of fixed costs and hospital overheads. Costs per units are estimated for both a teaching and a non-teaching hospital. A secondary analysis based on reimbursement fees will be performed. Other resource use (hospital days, outpatient visits and primary care) will be valued using standard prices (25).

In economic evaluations the preferred outcome measure for effectiveness is the quality adjusted life year. In obstetrics, the use of quality of life years as outcome measure might be less appropriate due to the relatively short duration of the delivery. As a result, many (cost) effectiveness studies focus on specific aspects of the delivery, such as pain relief and patient satisfaction (present proposal). These indicators are typically considered separately, but may be conflicting. In a HTA study additional to the present proposal (Development and validation of a delivery outcome measure. Principal investigator dr. [name], aanvraagnummer Projectnet 24349) a delivery-specific classification system consisting of several relevant but separate domains will be developed. The domain scores will be converted into a utility based, composite numerical index.

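### The protocol's only test for continuous outcomes is a rank test, which by default would judge the cost endpoint although the cost claim concerns mean cost per woman

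*Protocol*

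**What the plan says.** Protocol 8.1 first lists variables by type and then gives one rule for every continuous one: "Continuous variables will be tested with the Mann-Whitney U test". Kaplan-Meier is named for time to delivery only, and no other method for comparing continuous outcomes appears.

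Costs have a defined place in the plan. Section 6.1.2: "If RPCA is equivalent to EA with respect to pain appreciation the next endpoint will be the costs of both interventions". The same section says that costs "will be registered and compared (without discounting"), without naming an estimand, a test or an interval. The economic analysis text in 8.1 explains how resources are counted and priced, plans a secondary analysis on reimbursement fees, and includes items such as "neonatal care (admission to NICU/neonatology ward, outpatient visits"). It too names no statistical comparison.

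The introduction (section 1) shows what the cost result is for: "An estimation of costs for RPCA versus EA shows a decrease of 64 euro per patient", and then "Nationwide this could potentially save 1.2-4.6 million euro per year, depending on the percentage of women needing pain relief, varying respectively from 10-40" per cent. It adds: "It is expected that economical evaluation of both strategies will show a significant reduction in costs of this innovative strategy". The Summary gives cost-effectiveness as the objective; section 2 lists costs among the secondary objectives.

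**The concern.** The Mann-Whitney test asks whether a randomly chosen woman in one arm is as likely to cost more as to cost less than a randomly chosen woman in the other. That is not equality of mean costs. The two questions separate when costs are skewed and the arms differ in more than one component.

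The introduction attributes the expected saving to anaesthetic staff and nurses. That is a modest amount in most women who receive EA, and it shifts ranks. Neonatal or maternal admissions, if rare and expensive, carry much of the mean but hardly alter ranks. If RPCA saved the staff cost but led to a few more admissions, the stated test could show significantly lower costs while the average woman cost the same or more. The reverse error is also possible: a real mean difference produced by admissions could go undetected. At stake is the policy conclusion about cost savings, not the equivalence result on pain appreciation.

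**Working it through.** **1. The plan's own cost figure is a mean scaled up.** Inputs from section 1: 180,000 births a year, 64 euro per patient, 10% to 40% needing pain relief.
- 180,000 × 0.10 × 64 = 1,152,000 euro
- 180,000 × 0.40 × 64 = 4,608,000 euro

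These reproduce the stated 1.2 and 4.6 million. Multiplying a per-patient difference by a number of patients is valid for an arithmetic mean, not for a median or a rank statistic.

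**2. Numbers per arm (section 4.4).** 102 / (1 − 0.10 − 0.30)² = 283.3, rounded up to 284 per arm, so 568 treated. 568 / 0.5 = 1136 randomised, or 568 per arm. Both figures are reproduced.

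**3. A case with equal means.** Only the 64 euro comes from the protocol; the rest is assumed. Routine cost is lognormal with mean 2000 euro and SD 200, 300, 600 or 1000. An expensive admission has mean cost 6400 euro and probability 3%, with 1 percentage point more in women who receive RPCA.
- Difference in means, all women treated as allocated: −64 + 0.01 × 6400 = 0 euro
- All randomised, half treated: −64 × 0.5 + 0.005 × 6400 = 0 euro
- With 10% and 30% cross-over, treated women: −64 × 0.6 + 0.006 × 6400 = −38.4 + 38.4 = 0 euro

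The means are equal throughout. What the rank test picks up is the shift in routine cost. With cross-over this is 38.4 euro among treated women, or 38.4/200 = 0.19 SD at the smallest SD and 38.4/1000 = 0.04 SD at the largest.

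**4. Simulated rate of significant Mann-Whitney results at equal means** (two-sided 0.05; ranges are across repeated runs; admission costs gamma-distributed):

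| Routine SD (euro) | 284 per arm, no cross-over | 284 per arm, planned cross-over | 568 per arm, half treated, no cross-over | 568 per arm, half treated, planned cross-over |
|---|---|---|---|---|
| 200 | 91% | 50% | 62-67% | 27-30% |
| 300 | 57-59% | 25-26% | 32-35% | 14-16% |
| 600 | 16-18% | 9% | 11-13% | 6-7% |
| 1000 | 9-11% | 6-7% | 5-8% | 5-6% |

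Without cross-over, almost all of the rejections favour RPCA. A Welch comparison of means rejects in 4-6% in the same no-cross-over settings. At a routine SD of 2000 euro the Mann-Whitney rate without cross-over is 6-8%.

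**5. RPCA truly dearer.** Doubling the extra admissions makes RPCA dearer by −64 + 0.02 × 6400 = 64 euro per treated woman. Without cross-over, at 284 per arm, Mann-Whitney still declares RPCA cheaper in 85%, 48%, 13% and 7% of trials at SD 200, 300, 600 and 1000; Welch does so in about 1%. These figures ignore cross-over, so they show the direction of the error rather than its size in this trial.

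**6. Sensitivity to the tail.** Replacing the gamma tail by a fixed event of 5,000 or 10,000 euro gives 54-62% at SD 300 and 18-21% at SD 600 (equal means, 284 per arm, no cross-over, RPCA declared cheaper). The conclusion does not hinge on the form of the tail.

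**The case against.** The strongest reply is that the protocol never assigns the Mann-Whitney test to costs. The rule follows a list of typed variables in which total cost does not appear, and costs have their own heading, which names no test. On that view the method is simply unspecified and belongs in a statistical or health-economic analysis plan, which was not available here. Part of this stands: the rule reaches costs by default and not by express assignment, and a separate plan may specify a mean-based comparison. But the rule is worded for continuous variables without exception and nothing removes costs from it, so a separate plan using means would depart from 8.1 as written.

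Second, 8.1 also plans a decision analysis to choose between the strategies, and the expected significant reduction is a remark in the introduction, not a decision rule. That weakens the concern. It does not remove it, since the protocol does not say how costs enter the decision analysis.

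Third, a reader might infer from the columns without cross-over that a false finding of savings is likely in this trial. The documents do not support that. The cost distribution and the offsetting excess of RPCA admissions are assumed, and the protocol's own cross-over allowance cuts the rates sharply. A routine SD of 200-300 euro on a mean of 2000 is a coefficient of variation of only 10-15%, which is hard to square with costs that include mode of delivery, hospital stay and primary care.

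Fourth, one might infer that hospital days and visit counts should leave the rank rule as well. They are listed in 8.1 as variables in their own right, and a rank comparison of them as such is acceptable.

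**Conclusion.** The concern holds as a mismatch between the stated test and the quantity claimed. The protocol's cost argument is about mean cost per woman; the only test it states that could apply to costs is about ranks; the two can disagree in direction. This mismatch depends on no assumed distribution.

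Its size does, and cannot be derived from the protocol. Under the assumptions above and the planned cross-over, the rate of significant results at equal means lies between near nominal (5-9% at routine SD 600-1000 euro) and about 14-50% (SD 200-300 euro). The documents support saying that the error can occur, not how often it would occur here. It should be corrected because costs are the next endpoint after equivalence and carry the policy claim. The sample size, which rests on pain appreciation, is not affected.

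**What to change.** In 8.1, exempt total costs from the Mann-Whitney rule. State that arithmetic mean cost per woman will be compared between the randomised arms by intention to treat, and that the mean difference will be reported with a 95% confidence interval, for example from a bootstrap that respects the centre and parity strata used in the randomisation (section 6.2). Base any statement on cost savings on that interval. The Mann-Whitney test may stay for hospital days and visits as separate outcomes.

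The cost is one sentence and a short program, with no extra data or women. The drawback is that the interval for mean cost may be wide, so the expected significant reduction may not be shown.
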